### Modified disability in the physically active scale

The Disablement in the Physically Active Scale (DPA) [59] is a generic 16-item patient-reported outcome instrument that assesses physical and psychosocial status for physically active adults. A modified version of this instrument was restructured to separate the items into a psychosocial (Mental Composite Score) and a physical component (Physical Composite Score) [60]. Each item is scored on a 4-point Likert scale with 0 indicating *no problem* and 4 indicating *severely affected*. Although the items are the same as the original, the two components are scored independently. Thus, the Physical and Mental Composite Scores range from 0 to 48 and 0 to 16, respectively, with higher scores indicating greater disability. Adequate internal consistency was demonstrated for both the Physical (*α* = 0.941) and Mental Composite Scores (*α* = 0.878). The minimal detectable change scores of the Physical and Mental Composite Scores in individuals with CAI is 7 and 3 points, respectively [23].

### Fear avoidance beliefs questionnaire

The Fear-Avoidance Beliefs Questionnaire-Physical Activity subscale is designed to assess fear avoidance beliefs associated with physical activity in patients who are injured or who have a history of injury. This is a 5-item instrument scored on a 7-point scale with responses ranging from ‘*completely disagree*’ to ‘*completely agree*’. Scores range from 0 to 24 with a higher score representing increased fear avoidance [61]. This instrument has previously demonstrated sound clinometric properties including strong internal consistency and test–retest reliability (*a* = 0.77–0.96) with a minimal detectable change of 4 points in those with CAI [62, 63].

### Power analysis

The primary comparisons for all aims are the comparisons between FIRE and SOC groups at 6 months for the CAIT (Aim 1), posteromedial reach direction of the SEBT (Aim 2), and the Foot and Ankle Ability Measure Sport (Aim 3). A two-sample t-test comparing the change score between the FIRE and SOC groups will have at least 95% power to detect an effect size of 0.6 between the group means when the sample size is 150 (75 per group), assuming a two-sided significance level of 0.05. In the case that attrition reaches 40%, the sample size will still allow for 80% power to detect the same effect.

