Study type	Allocation: Randomized; Intervention Model: Parallel Assignment; Intervention Model Description:The investigators will compare clinical and innovative outcome measures collected at five time points between cohorts of patients with CAI that receive a standard of care (SOC) rehabilitation program compared to an innovative foot intensive rehabilitation (FIRE) program to determine if FIRE can further reduce the rate of re-injury, improve sensorimotor function, and reduce self-reported disability during the 24 months following the intervention.; Masking: Single (Outcomes Assessor); Masking Description: The investigators collecting the outcomes will be blinded to group allocation. Separate investigators will be used for intervention delivery and outcomes assessment. Primary Purpose: Treatment
Date of first enrolment	October 2021
Target sample size	150
Recruitment status	Recruiting
Primary outcome(s)	Number of recurrent ankle sprains [Time Frame: 24 months]: The ability of FIRE to attenuate the occurrence of ankle sprains compared to SOC rehabilitation will be determined through self-report. An ankle sprain will be operationally defined as an incident in which the rearfoot was inverted or supinated and resulted in a combination of swelling, pain, and time lost or modification of normal function for at least one day Frequency of episodes of the ankle giving way [Time Frame: 24 months]: The ability of FIRE to attenuate the number of episodes of the ankle giving way compared to SOC rehabilitation will be determined through self-reported occurrences per week in the past month. Episodes of giving way will be operationally defined for the patient as an incident in which the rearfoot suddenly rolled, felt weak, or lost stability; however, the individual did not sustain an ankle sprain and was able to continue with normal function Severity of chronic ankle instability related symptoms [Time Frame: 24 months]: The ability of FIRE to attenuate the severity of related symptoms compared to SOC rehabilitation will be determined through the Cumberland Ankle Instability Tool. The Cumberland Ankle Instability Tool is a 9-item instrument used to identify self-reported impairments associated with CAI. This instrument is scored on a 0–30 scale, where lower scores represent greater severity of CAI related symptoms

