Key secondary outcomes	Postural Control [Time Frame: 12 months]: The ability of FIRE to improve static and dynamic postural control compared to SOC rehabilitation will be determined. Multiple measurements will be made including: Single-limb stance on each limb with eyes open and eyes closed with use of a force plate for center of pressure measurements, Star Excursion Balance Test, forward jump single limb landing stabilization task. All measurements will be monitored while the patient wears an inertial sensor placed on the lumbar spine Ankle/Toe Strength [Time Frame: 12 months]: The ability of FIRE to improve strength compared to SOC rehabilitation will be determined. Strength of the muscles surrounding the ankle and the toes will be assessed through a series of assessments with a digital handheld dynamometer Intrinsic Foot Muscle Activation [Time Frame: 12 months]: The ability of FIRE to improve foot muscle activation compared to SOC rehabilitation will be determined. Abductor hallucis, flexor digitorum brevis, quadratus plantae, and flexor hallucis brevis functional activity ratios will be captured using diagnostic ultrasound with a 12–4 MHz linear array transducer probe and measured using Image J software Plantar Cutaneous Sensation [Time Frame: 12 months]: The ability of FIRE to improve plantar cutaneous sensation compared to SOC rehabilitation will be determined. Plantar cutaneous sensation will be tested using a 20-piece Semmes–Weinstein Monofilament kit which has monofilaments ranging from to 0.008 g of force (1.65 level) to 300 g of force (6.65 level). Light touch detection thresholds will be assessed on the plantar surface at the 1st metatarsal head

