### Primary outcomes

#### Recurrent ankle sprain and episodes of giving way

The number of recurrent ankle sprains since the previous testing session and the average number of ankle giving way episodes per week over the past month will be assessed through self-reporting. An ankle sprain will be operationally defined as an incident in which the rearfoot was inverted or supinated and resulted in a combination of swelling, pain, and time lost or modification of normal function for at least one day [37]. Episodes of giving way will be operationally defined as an incident in which the rearfoot suddenly rolled, felt weak, or lost stability; however, the individual will not have sustained an ankle sprain and was able to continue with normal function.

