### Statistical plan and data analysis

Continuous variables will be summarized with descriptive statistics and categorical variables will be summarized with counts and percentages. Change scores and percent change scores will be calculated from baseline for follow-ups at post-intervention, 6-, 12-, and 24-months; the primary outcome for all aims is the 6-month change score. Simple comparisons between groups will be performed using two-sample t-tests for continuous variables and chi-square tests of independence for categorical variables. Effect sizes will be interpreted as weak (≤ 0.39), moderate (0.40–0.69), or strong (≥ 0.70). A two-sided significance level of 0.05 will be used for all statistical tests. All analyses will be completed with SAS v9.4 (SAS Institute, Cary, NC, USA).

Although groups will be randomly assigned, potential covariates will be examined with bivariate analyses, and comparisons requiring covariate adjustment will use regression modeling (e.g. ANCOVA, logistic regression); unadjusted and adjusted estimates will be presented with 95% confidence intervals. Potential covariates include: baseline outcome values, demographic variables (e.g., sex, age, height, weight, data collection site), prognostic indicators (e.g., number of previous ankle sprains, frequency of episodes of giving way, Identification of Functional Ankle Instability score), and intervention compliance (% sessions completed).

To examine the trajectory over time and whether the groups change differently over time, mixed model approaches may be used. Comparisons between groups, time points, and the interaction of group and time will be made using linear mixed models or generalized linear mixed models, as appropriate. Mixed model analyses allow for a repeated measures approach with flexibility in variance–covariance structure while also providing estimates in the presence of potential covariates. Unadjusted and adjusted estimates will be provided by condition and time; significant group-time interactions will allow for presentation of results by condition for each time point. While the primary analyses across all aims will be the comparison of group means, the analyses for Aim 1 will additionally include the estimation of recurrent ankle sprain rates at 6, 12, and 24-months for the FIRE and SOC conditions. Moreover, time to recurrent injury will also be examined.

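### The protocol designates two different sets of primary outcomes that share only the CAIT, and the stated power covers only one of them

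*Protocol article*

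**What the plan says.** Two designations stand side by side in the current text.

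*First set.* The primary-outcome row of Table 1 (Summary and design) has three entries: "Number of recurrent ankle sprains [Time Frame: 24 months", "Frequency of episodes of the ankle giving way [Time Frame: 24 months" and "Severity of chronic ankle instability related symptoms [Time Frame: 24 months", the last measured by the Cumberland Ankle Instability Tool (CAIT). The Primary outcomes section of the body describes the same three. It collects the first two by self-report: "The number of recurrent ankle sprains since the previous testing session and the average number of ankle giving way episodes per week over the past" (the quote breaks off before the recall period for giving-way, which is one month). The CAIT follows under the same heading.

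*Second set.* The Power analysis section states: "The primary comparisons for all aims are the comparisons between FIRE and SOC groups at 6 months for the CAIT (Aim 1", and continues with "posteromedial reach direction of the SEBT (Aim 2), and the Foot and Ankle Ability Measure Sport (Aim 3". The Statistical plan and data analysis section adds that "the primary outcome for all aims is the 6-month change score". That sentence fixes a time point and names no instrument.

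The SEBT and the FAAM are both described after the Secondary outcomes heading. Table 1 places the SEBT within a key secondary entry, "Postural Control [Time Frame: 12 months". The analysis section treats recurrent sprain rates at 6, 12 and 24 months as an addition to the Aim 1 group-mean comparison, and says that time to recurrent injury will also be examined.

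**The concern.** A confirmatory trial needs one agreed statement of what decides it. Here a reader of Table 1 and the outcomes section would look to sprains, giving-way and the CAIT. A reader of the power section would look to the CAIT, SEBT reach and FAAM-Sport at 6 months. If these results disagree, for example a 6-month gain in FAAM-Sport with no difference in sprains over 24 months, the text supports reporting either as the primary result. All tests use two-sided 0.05, so the significance rule does not rank the claims either.

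The stakes are substantive because the central hypothesis in the Background opens with fewer future sprains and giving-way episodes. Those are the two outcomes that carry the primary label without a sample-size basis.

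**Working it through.** **1. Designations side by side**

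| Outcome | Table 1 | Outcome sections | Power analysis |
|---|---|---|---|
| Recurrent sprains | Primary, 24 months | Primary | Not named |
| Giving-way frequency | Primary, 24 months | Primary | Not named |
| CAIT | Primary, 24 months | Primary | Primary comparison, 6 months |
| SEBT posteromedial reach | Within postural control, key secondary, 12 months | Secondary | Primary comparison, 6 months |
| FAAM-Sport | Not in the outcome rows shown | Secondary | Primary comparison, 6 months |

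Distinct outcomes called primary: 3 + 3 − 1 shared = 5. On both lists: 1 of 5, the CAIT.

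**2. The plan's own power figure**

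Inputs from Power analysis: two-sample t-test on change scores, effect size d = 0.6, two-sided α = 0.05, 75 per group. With 40% attrition, 150 × 0.60 = 90 patients remain, or 45 per group.

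Normal approximation: power = Φ(d·√(n/2) − 1.96).

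- n = 75: 0.6 × √37.5 = 3.674; 3.674 − 1.96 = 1.714; Φ = 95.7%. Noncentral t: 95.5%. Stated: at least 95%.
- n = 45: 0.6 × √22.5 = 2.846; 2.846 − 1.96 = 0.886; Φ = 81.2%. Noncentral t: 80.4%. Stated: 80%.

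The arithmetic is right. The problem lies in which outcomes it is attached to.

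**3. Does that calculation reach sprains and giving-way?**

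Sprains are counted since the previous testing session, so there is no evident baseline value from which to form a change score. Giving-way is a weekly frequency, for which a change score could be formed, and an effect size of 0.6 could formally be applied to it. The power section does not name it, however. No sprain rate, treatment effect or power is given anywhere in the article.

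**4. Illustration only**

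Assume that sprain is reduced to any versus none, that FIRE halves the SOC risk, and that the SOC risk lies between 20% and 50%. None of these assumptions comes from the document. With p̄ = (p₁ + p₂)/2, power = Φ{[(p₁ − p₂) − 1.96·√(2p̄(1 − p̄)/n)] / √[(p₁(1 − p₁) + p₂(1 − p₂))/n]}.

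Example, 30% against 15% with n = 75: p̄ = 0.225, null standard error 0.0682, alternative standard error 0.0671; (0.15 − 1.96 × 0.0682)/0.0671 ≈ 0.24; Φ ≈ 60%.

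| Assumed SOC risk | 75 per group | 45 per group |
|---|---|---|
| 20% | 40% | 26% |
| 30% | 60% | 40% |
| 40% | 77% | 55% |
| 50% | 89% | 69% |

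The range is wide. It shows that the stated 95% and 80% cannot be carried over to sprains. It does not show what the trial's power for sprains is.

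**The case against.** The best defence is that the power section picks one lead variable per aim for sizing, while Table 1 and the outcomes section classify the outcomes. This explains why Aims 2 and 3 each have a named variable, but it does not remove the conflict. The section calls these the primary comparisons, SEBT and FAAM remain under Secondary outcomes, and the analysis section makes the 6-month change score primary for all aims while sprain rates are an addition.

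Other points stand and limit the claim:

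- The 24 months in Table 1 may be a collection window, since the same table describes five time points over 24 months of follow-up. A reader might infer a firm clash of time points for the CAIT. The text allows that reading but does not compel it.
- A reader might infer that FAAM is unregistered. The Table 1 row covers key secondary outcomes and may be a subset, and the registry record is not at hand.
- A reader might take sprains as the lead registered outcome because they come first. Table 1 ranks nothing.
- The sprain figures reduce a count to yes or no and depend on assumed risks. A count or time-to-event analysis could differ, and at higher SOC risks the power is better. The 45-per-group case may also be too pessimistic for Aim 1, whose outcomes can be collected electronically to limit attrition.
- Removing the primary label from sprains or giving-way during recruitment is itself a substantive change, and not the only defensible one.

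**Conclusion.** The conflict of designation is real and rests on the wording alone. Table 1 and the Primary outcomes section agree with each other and disagree with the Power analysis section on two of three members. The stated power reproduces but does not cover sprains or giving-way. Which result decides the trial is therefore open.

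A reader might go further and call this outcome switching. The document does not support that: Table 1 gives the status as recruiting, no results are reported, and nothing has been switched. What exists is room for selective reporting, which can still be closed. The conclusion needs no assumed sprain rate, and it does not depend on reading the 24-month time frame as an analysis time point.

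**What to change.** By a dated amendment before any unblinded comparison, state one primary outcome and one time point, and make Table 1, the outcomes sections, the Power analysis section and the Statistical plan and data analysis section agree. Table 1 should say whether its time frames are collection windows or analysis time points.

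CAIT change at 6 months is the natural candidate, because it is on both lists and the power statement already covers it. SEBT posteromedial reach and FAAM-Sport at 6 months would then be labelled the lead secondary comparisons for Aims 2 and 3.

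If the sponsor prefers to keep sprains or giving-way primary, the protocol should say that the stated power does not apply to them, and give their analysis and time point.

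The cost is a protocol and registry amendment, with the reason recorded, and possibly the loss of a primary label for some outcomes. No change to data collection or sample size follows from the CAIT option.

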### Statistical plan and data analysis

Continuous variables will be summarized with descriptive statistics and categorical variables will be summarized with counts and percentages. Change scores and percent change scores will be calculated from baseline for follow-ups at post-intervention, 6-, 12-, and 24-months; the primary outcome for all aims is the 6-month change score. Simple comparisons between groups will be performed using two-sample t-tests for continuous variables and chi-square tests of independence for categorical variables. Effect sizes will be interpreted as weak (≤ 0.39), moderate (0.40–0.69), or strong (≥ 0.70). A two-sided significance level of 0.05 will be used for all statistical tests. All analyses will be completed with SAS v9.4 (SAS Institute, Cary, NC, USA).

Although groups will be randomly assigned, potential covariates will be examined with bivariate analyses, and comparisons requiring covariate adjustment will use regression modeling (e.g. ANCOVA, logistic regression); unadjusted and adjusted estimates will be presented with 95% confidence intervals. Potential covariates include: baseline outcome values, demographic variables (e.g., sex, age, height, weight, data collection site), prognostic indicators (e.g., number of previous ankle sprains, frequency of episodes of giving way, Identification of Functional Ankle Instability score), and intervention compliance (% sessions completed).

To examine the trajectory over time and whether the groups change differently over time, mixed model approaches may be used. Comparisons between groups, time points, and the interaction of group and time will be made using linear mixed models or generalized linear mixed models, as appropriate. Mixed model analyses allow for a repeated measures approach with flexibility in variance–covariance structure while also providing estimates in the presence of potential covariates. Unadjusted and adjusted estimates will be provided by condition and time; significant group-time interactions will allow for presentation of results by condition for each time point. While the primary analyses across all aims will be the comparison of group means, the analyses for Aim 1 will additionally include the estimation of recurrent ankle sprain rates at 6, 12, and 24-months for the FIRE and SOC conditions. Moreover, time to recurrent injury will also be examined.

The primary analysis will be intent-to-treat (ITT), comparing groups as randomized. The ITT analysis will be performed using all randomized patients, where data for those terminated or lost to follow-up may be imputed using multiple imputation. If such methods are deployed, sensitivity analyses will be performed. Additional analysis will also be conducted comparing groups as they were randomized with data as observed. An attrition analysis will be conducted by comparing the demographics and outcomes measured at baseline in patients who completed follow-up to those who did not. Mechanisms for missing data will be investigated by comparing important covariates between patients with and without missing data at each time point. Furthermore, data on compliance measures will be captured within the weekly intervention logs, and a modified ITT may also be conducted but limited to those who achieved at least 75% of the intervention protocol across all six weeks. Ultimately, sensitivity analyses will be conducted comparing the results of our imputation methods to complete-case and available-data analyses. Throughout all ITT and as treated analyses, assumptions will be checked, and remedial measures will be deployed as needed.

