### Patients

One hundred and fifty men and women (*n* = 50 at each site) will be recruited from the campuses and surrounding communities associated with the University of Kentucky, University of Virginia, and Naval Hospital Camp Pendleton through posted flyers, social media postings, and word of mouth at local sports medicine clinics. The university-based sites are sports medicine laboratories located in suburban academic settings in Lexington, KY and Charlottesville, VA. The military site is an outpatient sports medicine clinic located at Marine Corps Base Camp Pendleton that provides specialized primary and referred care to military beneficiaries consisting primarily of US Marines and Navy Sailors. At all three sites, potential patients will be pre-screened by telephone or in-person by a local member of the research team using a checklist containing components of the inclusion and exclusion criteria. Patients who appear eligible based on prescreening and have continued interest in participating in the study will be scheduled to meet with a member of the research team who trained to perform the enrollment and informed consent process.

The procedures for assessing eligibility were derived and aligned with the guidelines for selecting CAI patients from the International Ankle Consortium [36]. To be included, patients must be a male or female adult, aged 18–44 years with a history of ≥ 1 ankle sprain. Patients must also report ≥ 2 episodes of “giving way” in the past 3 months. An ankle sprain will be defined as an injury in which the rearfoot was inverted or supinated and resulted in a combination of swelling, pain, and time lost or modification of normal function for at least one day [37]. Episodes of giving way will be described as an incident in which the rearfoot suddenly rolled, felt weak, or lost stability; however, the individual did not sustain an ankle sprain and will have been able to continue with normal function after the incident [37]. In addition, patients must answer “yes” to ≥ 5 questions on the Ankle Instability Instrument and ≥ 11 on the Identification of Functional Ankle Instability [38]. In cases of bilateral CAI, the limb with the higher Identification of Functional Ankle Instability score will be identified as the involved limb for intervention.

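### The change-from-baseline rule is applied to sprain and giving-way counts without exception, though sprains have no baseline value, and the named group tests carry no person-time

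*Protocol article*

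**What the plan says.** Table 1 of the Protocol article (section Summary and design) lists three primary outcomes for Aim 1. Two are counts or frequencies: "Number of recurrent ankle sprains [Time Frame: 24 months"] and "Frequency of episodes of the ankle giving way [Time Frame: 24 months"]. The third is the CAIT, also at 24 months.

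The section Recurrent ankle sprain and episodes of giving way defines how they are measured. Sprains are "The number of recurrent ankle sprains since the previous testing session". Giving way is a weekly average over the past month. Both are self-reported.

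The section Statistical plan and data analysis then says that "Change scores and percent change scores will be calculated from baseline for follow-ups at post-intervention, 6-, 12-, and 24-months" and that "the primary outcome for all aims is the 6-month change score". Simple group comparisons use t-tests for continuous variables and chi-square tests for categorical ones. The primary analyses for all aims compare group means. For Aim 1, sprain rates by condition at 6, 12 and 24 months are estimated in addition, and "time to recurrent injury will also be examined". Linear or generalized linear mixed models are optional.

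The section Power analysis names the CAIT at 6 months as the primary comparison for Aim 1.

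**The concern.** A change score needs the same quantity measured before and after. The sprain outcome is an interval count that starts at the first visit, so there is nothing to subtract. The rule is nevertheless written for all aims, and sprains come first among the listed primary outcomes. Someone applying the text literally would have to improvise, for example by subtracting lifetime sprain history, which is on a different scale and appears in the plan only as a candidate covariate.

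Giving way is different. Its baseline exists, so a simple change score exists. Percent change, which the same sentence prescribes, fails when the baseline is zero.

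The likely fallback for sprains is a t-test on counts or a chi-square test on any sprain. Neither uses length of follow-up. Reducing future sprains leads the trial's central hypothesis, so the method for this comparison should not be left to choice once the data are seen.

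**Working it through.** **1. The plan's own figure.** Power analysis: two-sample t-test on the change score, effect size 0.6, two-sided 0.05. By the noncentral t, 75 per group gives 95.5% (stated: at least 95%). With 40% attrition, 75 × 0.6 = 45 per group gives 80.4% (stated: 80%). Both reproduce. They concern a continuous change score and are not at issue.

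**2. Does a baseline exist on the same scale?**

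| Outcome | Measured as | Baseline value | Change | Percent change |
|---|---|---|---|---|
| Sprains | count since last visit | none | undefined | undefined |
| Giving way | weekly average, past month | yes, may be 0 | defined | undefined if baseline is 0 |
| CAIT | 0–30 score | yes | defined | defined if baseline is above 0 |

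**3. How often could baseline giving way be zero?** The entry rule in the section Patients is "Patients must also report ≥ 2 episodes of “giving way” in the past 3 months". The outcome looks back one month, so zero is allowed. If k episodes fall independently and evenly over the three months (assumption), P(none in the last month) = (2/3)^k:
- k = 2: 44%
- k = 3: 30%
- k = 4: 20%
- k = 6: 9%
- k = 12: under 1%

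The documents do not give the distribution of k.

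**4. Length of the counting intervals.** From the section Procedures, the post-intervention visit comes about 6 to 8 weeks after baseline (6 weeks of treatment, plus up to one week on either side). The later visits are at about 6, 12 and 24 months. The intervals are therefore about 1.5–2, 4–4.5, 6 and 12 months. A missed visit lengthens the next interval. A 6-month sprain total needs the first two counts added together.

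**5. Raw counts under unequal dropout (assumed).** Equal true rates, 40% against 20% dropout, leaving at 12 months on average, partial counts kept:
- 24 − 0.40 × 12 = 19.2 months
- 24 − 0.20 × 12 = 21.6 months
- 19.2 / 21.6 = 0.889, an apparent 11% reduction from no effect

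**6. Simulation (assumed inputs).** 75 per arm; 24 months; 0.3 to 1.0 sprains per person-year; gamma dispersion 0.5 to 1.0; dropouts leave at month 6 or 12 with their counts kept; 1,500 runs per setting. The person-time test uses the log ratio of total count to total person-time with a robust variance. Dropouts leave at 9 months on average here, so the follow-up ratio at 40% against 20% is (24 − 0.40 × 15) / (24 − 0.20 × 15) = 18 / 21 = 0.857. Rejection rates across settings:

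| Setting | t-test on counts | Person-time rate test |
|---|---|---|
| No effect, 20% dropout in both arms | 3.8–5.5% | 4.5–5.9% |
| No effect, 20% vs 40% | 7.1–14.1% | 5.0–6.2% |
| Rate ratio 0.6, 20% in both arms | 36–74% | 38–77% |
| Rate ratio 0.6, SOC 40%, FIRE 20% | 18–40% | 35–76% |

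The simulation standard error at 5% is √(0.05 × 0.95 / 1500) = 0.6 points.

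**The case against.** The strongest reply is that the Power analysis section makes the CAIT the Aim 1 primary comparison. The change-score sentence may then have been meant only for the CAIT, the SEBT and FAAM Sport, for which it works. That is a plausible reading, but the sentence is not so limited, and Table 1 still lists sprains and giving way as primary at 24 months. The sections need reconciling either way.

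A second reply is that model detail such as links and offsets belongs in an analysis plan that is not shown. That is fair for missing detail. The point here is a rule that the article states and that cannot be applied to one of its outcomes.

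Third, both arms share one visit schedule, a later completed visit covers a missed one, and Aim 1 outcomes can be collected electronically. This stands: unequal intervals alone do not bias the comparison of arms. Unequal dropout could, and nothing in the article predicts that it will occur. The 40% in the Power analysis section is an overall contingency.

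A reader might infer three stronger claims. The article does not support them:
- **That follow-up time is ignored throughout.** Sprain rates, time to injury, optional generalized linear mixed models and optional multiple imputation are all named.
- **That time to re-injury is not captured.** The article describes counts per interval, but sprain dates may be on forms it does not reproduce.
- **That the sprain outcome cannot be computed.** Counts and rates can be; only the change score cannot.

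**Conclusion.** The point holds in a limited form. The change-score rule is undefined for sprains in all 150 patients. Percent change in giving way is undefined whenever the past-month baseline is zero: 44% of the time at the entry minimum under even spread, falling quickly with more frequent episodes. The simple change score for giving way is sound.

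No group comparison of sprains that uses person-time is fixed. Under the assumed 40% against 20% dropout, raw counts show an 11% spurious difference, and the t-test rejects a true null in 7–14% of trials. With equal dropout it stays near 5%, and the two tests have similar power. These sizes rest on assumed rates, dispersion and dropout, none of which the article gives. The sample-size figures are unaffected.

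**What to change.** - Restrict change and percent change to continuous scores with a baseline (CAIT, SEBT, FAAM Sport and similar).
- Reconcile Table 1, Power analysis and Statistical plan and data analysis on which Aim 1 outcome is primary and at what time.
- Compare sprains between arms with a count model, for example negative binomial, with group, site and a log person-time offset. Report the rate ratio with its 95% interval at 6, 12 and 24 months. The offset corrects for unequal follow-up provided that dropout is unrelated to sprain risk given the model, so keep the planned missing-data sensitivity analyses.
- Analyse giving way with adjustment for baseline frequency, and drop its percent change.
- For time to re-injury, use sprain dates if they are recorded; otherwise use an interval-censored method.

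The cost is a change of wording and a little more analysis work. If sprain dates are not already collected, asking for them would add one field to an existing questionnaire. Enrolment began in October 2021, so this should be settled before any unblinded analysis.
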